### Eligibility criteria

Adults with T2DM 18–45 years of age who were diagnosed less than 6 years previously, are not on insulin therapy, and who have a HbA1c value between 6% and 10% if taking other glucose-lowering medication or between 6.5% and 10% if not taking any glucose-lowering medications. Eligibility criteria are detailed in table 2.

**Table 2 T2:** Inclusion and exclusion criteria

Inclusion criteria	
Age	18–45 years, inclusive
Type 2 diabetes	Physician diagnosis more than 3 months and less than 6 years previously
Haemoglobin A1c	6.5%–10%, inclusive if not taking glucose-lowering medication; 6%–10% if taking glucose-lowering medication
Body mass index	30 kg/m^2^* to 45 kg/m^2^, inclusive if White or Indigenous† 27 kg/m^2^* to 45 kg/m^2^, inclusive if other background, including mixed
Weight stability	Weight changes of less than 5 kg over the prior 6 months
Walking ability	Able to walk without assists and to participate in structured exercise training requiring the lower limbs
Capacity	Able to understand written and spoken English and/or French Able to provide informed consent
Willingness	Willing to be randomised and able to participate Willing to attend supervised exercise sessions, if so randomised Willing to adopt low energy diet, including abstinence from alcohol, if so randomised Willing to self-monitor glucose and blood pressure at the required frequency, if randomised to the low energy diet plus supervised exercise arm
Exclusion criteria	
Other diabetes types	Type 1 diabetes Gestational diabetes Monogenic diabetes
Poorly controlled blood pressure	Resting systolic blood pressure greater than 150 mm Hg or resting diastolic blood pressure greater than 90 mm Hg diastolic
Weight loss interventions	Currently participating in a weight reduction programme in addition to routine care. Previous bariatric surgery.
Medications	Insulin therapy* Use of licensed weight loss medications Significant changes in glucose lowering medications in the prior 3 months, as judged by study physicians Steroids by mouth or injection
Self-reported allergies to components of meal replacement products	Milk protein and/or other relevant allergies
Dietary practices	Dietary practices that prohibit the use of meal replacement products
Pregnancy and lactation	Pregnancy Lactation Planning to become pregnant in the next 8 months
Eating disorder	Self-reported or diagnosed
Substance abuse	Alcohol, drugs
Estimated glomerular filtration rate	Less than 60 mL/min per 1.73 m^2^

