#### Partial meal replacement low energy diet and supervised exercise (weeks 3–12 inclusive)

##### Exercise physiologist

Starting at week 3, an exercise physiologist supervises 2 weekly sessions with aerobic and resistance components, at a designated facility. A third session is aerobic only, on site or elsewhere, as preferred, with self-monitoring (heart rate monitor and/or physical activity tracker provided). Participants increase exercise intensity and duration over time, with a goal of 60 min sessions.

Aerobic exercise on-site includes brisk treadmill walking (60%–80% of the maximum stress test heart rate). There is a high intensity interval walking option,^49^ to maximise improvements in fitness, insulin sensitivity^50^ and lean mass preservation.^51 52^ With walking challenges (eg, plantar fasciitis), cycle ergometer may be offered.

Resistance training with machines or free weights includes one to three sets of four upper body exercises (bench press, seated row, shoulder press and pull down), three leg exercises (leg press, extension, flexion) and exercises targeting stability, function and posture, with a goal of 8–12 repetitions per set. At 12 repetitions with good technique, the prescribed resistance is increased. Participants are instructed in resistance band use, in preparation for the maintenance phase.

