### Control group

The control group receives care from their usual physician, in accordance with National Institute for Health and Care Excellence^53^ and Diabetes Canada^54^ guidelines. Following final evaluations, control arm participants will be offered a 12-week low energy diet intervention followed by a 4-week food reintroduction period.

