### Statistical analyses

Our primary outcome measures the proportion of remission in the intervention arm relative to the control arm. We will apply intention-to-treat principles for the primary outcome, assuming that remission of diabetes did not occur if information is not available. Based on the DiRECT and DIADEM-I trials, we estimate that remission counts in the control arm could be less than 2. We will therefore use stratified Fisher’s exact test statistics (ie, stratification by country and by sex) if remission counts are low in the control arm but consider Pearson χ^2^ test, if appropriate. If numbers permit, logistic ORs with 95% CIs (exact method) will also be performed to further quantify the efficacy of intervention over the control group, after adjusting for factors used to stratify the randomisation (country, age or sex); we will not have missing values for these covariates. Subgroup analyses for the primary outcome will be performed by country, sex and the degree of weight loss (<5%, 5%–10%, 10%–15%, >15% as examined in the DiRECT trial,^9^ collapsing categories as needed, and by exercise adherence (<50%, >50% of supervised sessions attended). In a per-protocol analysis, we will restrict the intervention group to those who achieved at least 10% wt loss and adhered to at least two thirds of prescribed exercise sessions.

We will analyse dichotomous secondary outcomes (eg, diabetes remission at 12 weeks, hypertension remission at 12 and 24 weeks) as described for the primary outcome. We will analyse continuous key secondary outcomes (eg, left ventricular peak early diastolic strain rate, lean soft tissue mass) through linear regression or log-linear regression, as appropriate, with stratification by country and sex.

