## Discussion

Low energy diets incorporating meal replacements can achieve T2DM remission through weight loss,^9–11^ but may reduce lean mass.^18 19^ Exercise can preserve lean mass^18 19^ and directly lower insulin resistance.^13 20 50 59 60^ Combined aerobic and resistance training yields additive glucose-lowering benefits.^20^ Regular exercise reduces CVD events^61–64^ and improves MRI-based measures of heart health.^18^ RESET for REMISSION will quantify remission of T2DM in young adults achieved through a combined low energy diet and supervised aerobic and resistance training intervention and will also ascertain changes in diastolic function, lean mass and other factors that may impact long term outcomes.

Since funding was awarded for RESET for REMISSION, the literature has continued to evolve, with publication of the DIADEM-I trial, which targeted remission in younger adults less than 50 years of age of West Asian or North African ancestry. DIADEM-I combined a low energy diet (800–820 kcal/day) with exercise prescription from a trained professional centred on walking activities and self-monitoring tools, with resistance exercises introduced as the intervention progressed. While this trial did not include supervised exercise training, the objective measurement of physical activity, or cardiac function and structure, it does provide robust evidence that a low energy diet combined with physical activity can be combined in younger adults with T2DM while leading to an equivalent level of remission as has been shown in older populations, such as DiRECT.

While young persons with T2DM stand to gain the most from remission,^24^ their daily life demands may render recruitment and adherence challenging. We have endeavoured to mitigate this by integrating virtual communication tools for monitoring and follow-up where possible. Recruitment itself may be challenging in these younger individuals, as they remain fewer in number than middle-aged and older individuals with T2DM.^27^ We are, therefore, collaborating with a wide network of practices and drawing on other diabetes research cohorts in which participants have provided permission to be contacted for trials.

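### Weight loss and supervised-session attendance are listed as subgroups of the between-arm primary outcome, but neither can give a valid subgroup treatment effect

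*Protocol article*

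**What the plan says.** The Statistical analyses section sets the primary contrast between arms: "Our primary outcome measures the proportion of remission in the intervention arm relative to the control arm". Later in the same paragraph it states: "Subgroup analyses for the primary outcome will be performed by country, sex and the degree of weight loss". The weight-loss bands (<5%, 5%–10%, 10%–15%, >15%) are described "as examined in the DiRECT trial" and may be merged where necessary. The same sentence adds a further subgroup, "by exercise adherence (<50%, >50% of supervised sessions attended". All four factors share one label. Nothing confines the last two to the intervention arm, calls them descriptive or names a comparator.

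Elsewhere in the article:

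- **Control group:** "The control group receives care from their usual physician".
- **Eligibility criteria (table 2):** candidates must be "Willing to attend supervised exercise sessions, if so randomised".
- **Exercise physiologist (under Experimental group):** from week 3, "an exercise physiologist supervises 2 weekly sessions with aerobic and resistance components".
- **Outcomes (table 1):** weight and BMI are key secondary outcomes at weeks 12 and 24.
- **Discussion:** low energy diets with meal replacements "can achieve T2DM remission through weight loss".

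**The concern.** A treatment-effect subgroup must be defined by something that treatment cannot change and that is known in both arms. Country and sex meet this, and they also stratify the randomisation. The other two factors do not.

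- **Attendance** has no value in the control arm, so no between-arm contrast exists within an attendance group. Setting attenders against all controls compares a self-selected part of one arm with the whole of the other.
- **Weight loss** has a value in both arms but is produced by the intervention. A control who loses 5%–10% on usual care is not the counterpart of an intervention participant who loses the same on an 800–900 kcal diet. The within-band contrast also removes whatever part of the effect acts through weight loss.

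What is at stake is interpretation. Numbers set out as subgroup results beside country and sex invite the reading that the intervention works better in some people than in others, and the trial is meant to inform the planning of a later effectiveness study.

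**Working it through.** The article gives no figure for these analyses, so there is none to reproduce. The check sets the four factors side by side and then illustrates the consequences under stated assumptions.

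**Step 1. Do the factors qualify?**

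| Factor | Fixed before randomisation? | Defined in controls? | Can treatment change it? |
|---|---|---|---|
| Country | yes | yes | no |
| Sex | yes | yes | no |
| Weight loss | no | yes | yes (an outcome in table 1; a route to remission in the Discussion) |
| Supervised-session attendance | no | no | exists only under treatment |

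With 100 participants at 1:1 (Sample size section), each arm has 100/2 = 50, and 0 of 50 controls can be classified by attendance.

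**Step 2. Weight-loss bands, illustration.** Every input is an assumption and none comes from the article. Percentage weight loss is normal, with mean 1 and SD 3 in controls and mean 11 and SD 5 in the intervention arm. Expected controls per 50:

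- <5%: 50 × P(Z < (5−1)/3) = 50 × 0.909 = 45.4
- 5%–10%: 50 × 0.090 = 4.5
- 10%–15%: 50 × 0.0013 = 0.1
- >15%: 0

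The intervention arm splits 5.8 / 15.3 / 18.4 / 10.6.

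Log-odds of remission = −3.6 + 0.25 × weight loss + g × U + d × arm. U is a prognostic factor that also influences weight loss, and d is any effect of treatment not acting through weight loss. With 2,000,000 simulated participants, remission in percent (intervention vs control, difference in points) was:

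| Setting | Overall | <5% band | 5%–10% band |
|---|---|---|---|
| g=0, d=0 | 34.2 vs 4.3 (+29.9) | 5.3 vs 3.5 (+1.8) | 16.5 vs 12.0 (+4.5) |
| g=0.8, d=0 | 36.8 vs 6.7 (+30.1) | 3.2 vs 4.7 (−1.5) | 14.8 vs 26.1 (−11.3) |
| g=0, d=1 | 53.0 vs 4.3 (+48.7) | 13.4 vs 3.5 (+9.9) | 34.7 vs 11.9 (+22.8) |
| g=0.8, d=1 | 52.4 vs 6.8 (+45.6) | 7.9 vs 4.8 (+3.1) | 29.9 vs 26.2 (+3.7) |

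The band contrast does not recover the overall effect. Nor does it recover the part not acting through weight loss: with d = 1 in both of the last two rows, the 5%–10% contrast is +22.8 or +3.7 depending only on the shared prognostic factor. Merging bands changes the counts, not this behaviour.

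**Step 3. Attendance against all controls, illustration.** Again every input is assumed. Log-odds of remission = −3.3 + 2.9 × arm + r × U. Attendance depends partly on U and has no effect of its own on remission.

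| r | Overall difference | >50% attenders vs all controls | <50% attenders vs all controls |
|---|---|---|---|
| 0 | 40.2−3.6 = +36.6 | +36.5 | +36.7 |
| 0.5 | 40.7−4.0 = +36.7 | +40.2 | +29.0 |
| 1.0 | 41.8−5.3 = +36.5 | +42.6 | +22.8 |

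At r = 1 the gap is 42.6 − 22.8 = 19.8 points, although attending does nothing. Measured against the controls who would have fallen in the same attendance group, who can be identified only in a simulation, the differences are 41.4 and 25.6, a gap of 15.8. So most of the gap reflects who attends, and 19.8 − 15.8 = 4.0 points come from using the wrong comparator. None of it is an effect of attendance.

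**Step 4. What is untouched.** The primary test uses everyone as randomised, with missing remission counted as none. The sample size rests on arm-level remission rates and completion (for the initial design, 56/(1 − 0.30) = 80 recruited). Neither uses these subgroups.

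**The case against.** The strongest reply is that a descriptive analysis was meant all along. No within-band test, p-value or claim of effect modification is specified. Attendance can only sensibly be read within the intervention arm. The bands are borrowed from an earlier remission trial, which may have tabulated remission by weight loss descriptively. The per-protocol sentence that follows applies weight loss and exercise adherence to the intervention group only.

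Much of this stands. The within-arm reading is plausible, and an analysis plan not shown here may already state it. But the article does not say so. It places the two factors under the same label as country and sex, for an outcome that it has just defined between arms, and it writes an arm restriction only for the per-protocol analysis. The reference to the earlier trial explains the cut-points, not the comparison.

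Two further points are fair. The provision to merge bands answers part of the sparse-cell worry. The gap at exactly 50% attendance is minor: two weekly sessions over weeks 3–12 would make it 10 of 20, but the abstract speaks of supervised training three times weekly and maintenance can add supervised sessions, so the denominator is not settled.

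**Conclusion.** The point holds as a defect of specification. Followed as written, the attendance subgroups have no between-arm contrast (0 of about 50 controls classifiable), and the weight-loss subgroups give a biased one. This conclusion rests on the article's own description of the control arm, the supervised sessions and the role of weight loss, not on the simulations. Those show only that the distortion can be large, from a reduced difference to a reversed one, under assumed inputs.

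Stronger readings are tempting but unsupported:

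- **That the trial's main result is compromised.** The intention-to-treat test and the sample size do not depend on these subgroups.
- **That the trial will report these results as effect modification.** A reader might infer this, but the article does not say it.
- **That a particular number of controls will reach the upper weight-loss bands.** The article gives no figure for control weight loss.
- **That further baseline subgroups with interaction tests are required.** That would be a preference. The article allows that fewer than two controls may remit, so interaction terms would be close to non-estimable.

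**What to change.** In the Statistical analyses section, or in the analysis plan if it does not already say so:

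1. Keep country and sex as the only treatment-effect subgroups for remission.
2. Move weight loss and attendance to a separately labelled descriptive analysis within the intervention arm: remission counts and proportions by weight-loss band and by attendance group, stated to be non-causal, with no between-arm tests and no claims of effect modification.
3. Assign exactly 50% attendance to one of the two groups.

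The cost is a few lines of wording. No additional data, participants, subgroups or interaction tests are needed, and the primary analysis and the target of 100 stay as they are.

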### Sample size

In the DIRECT trial, remission was 46% at 1 year (vs 4% in control arm; OR 19.7).^9^ Even higher remission was observed over the shorter term in other studies.^57^ We initially allowed for a minimum 45% remission at 24 weeks in the intervention group and up to a 5% remission rate in the control group. Using a Fisher’s exact test with 90% power, a significance of 0.05, and a 1:1 ratio between intervention and control groups, we estimated needing 56 individuals to complete the trial (control=28, intervention n=28). Allowing for up to 30% drop-out, we planned to recruit 80 individuals in total (40 UK, 40 Canada) in our successful application for funding to the MRC and the Canadian Institutes of Health Research.

We subsequently obtained additional funding from the Canadian JR McConnell Foundation, and increased recruitment goals in Canada from 40 to 60 participants (40 UK, 60 Canada). With an overall sample size of 100 (40 UK, 60 Canada), if 70 (70%) complete the trial, we will have 90% power to detect a minimum 35% remission at 24 weeks in the intervention group and up to a 5% remission rate in the control group.

Retention of at least 35 participants in each arm (70 total) will provide over 80% power to detect a difference in mean peak early diastolic strain rate of 0.10/s difference, equivalent to the exercise effect in the DIASTOLIC trial (see BACKGROUND),^18^ assuming that the common SD is 0.144 as in the DIASTOLIC trial and using a two group t-test with a 5% two-sided significance level.

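### The per-protocol analysis selects intervention participants on 10% weight loss, a response to treatment, with no matching rule for controls, so it favours the intervention and can show an effect when there is none

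*Protocol article*

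**What the plan says.** The primary analysis of remission is by intention to treat: "We will apply intention-to-treat principles for the primary outcome, assuming that remission of diabetes did not occur if information is not available". The same section (Statistical analyses) then adds a per-protocol analysis, which will "restrict the intervention group to those who achieved at least 10% wt loss and adhered to at least two thirds of prescribed exercise sessions". Both conditions are observed after randomisation, and both apply to the intervention arm only. No condition is stated for controls.

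Three other places bear on this:

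- Control group: "The control group receives care from their usual physician". Controls have no study diet or study exercise sessions to adhere to.
- Discussion: "Low energy diets incorporating meal replacements can achieve T2DM remission through weight loss".
- Experimental group: what is prescribed is a diet with meal replacement products, visits to the dietitian and physician, and exercise sessions. The maintenance phase aims to hold whatever weight loss was reached. No 10% target is set anywhere in the intervention.

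**The concern.** A per-protocol set is meant to hold people who received the treatment as planned. The exercise condition is of that kind. The weight-loss condition is not. Someone who follows every element and loses 8% is excluded, while someone who attends two thirds of the sessions, neglects other elements and loses 10% is kept. Weight is also one of the trial's key secondary outcomes (Table 1).

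Because weight loss is tied to remission, the rule picks out the intervention participants most likely to remit and leaves the control arm unselected. Randomisation no longer protects the comparison, and the error runs in favour of the intervention. The Aims section says the results will guide a longer-term effectiveness trial. A reader who took the per-protocol figure as the effect of following the programme would expect too much of it.

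**Working it through.** **1. The plan's own figures.** The article gives no figure for the per-protocol analysis. The nearest are the initial sample-size assumptions: "minimum 45% remission at 24 weeks in the intervention group and up to a 5% remission rate in the control group", with a Fisher's "exact test with 90% power, a significance of 0.05, and a 1:1 ratio between intervention and control groups". For two proportions, n = [1.96√(2 × 0.25 × 0.75) + 1.2816√(0.45 × 0.55 + 0.05 × 0.95)]² / 0.40² = 22.5 per arm, and 28 after the continuity correction. That is 56 completers, and 56 / 0.70 = 80 recruited, as the article states. Exact two-sided Fisher power at 28 per arm is 0.933. The 5% control rate is carried into the check below.

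**2. A trial with no effect.** Inputs:

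- 50 per arm (100 in total, 1:1; Sample size).
- True remission p = 5% in both arms, the article's upper planning rate for controls.
- A share q of the intervention arm meets the per-protocol rule (assumption, 10% to 40%).
- Meeting the rule and remitting are linked by a latent normal correlation ρ (assumption, 0.3 to 0.8).

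With a = Φ⁻¹(1 − p) and b = Φ⁻¹(1 − q), remission among those who qualify is Φ₂(−a, −b; ρ) / q. The rejection rate is an exact enumeration of the two-sided, unstratified Fisher test at 0.05, comparing 50q qualifiers with all 50 controls.

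| q (number kept) | ρ | Remission, kept vs control | Odds ratio | Rejects |
|---|---|---|---|---|
| 10% (5) | 0.3 | 12.3% vs 5% | 2.7 | 7% |
| 10% (5) | 0.5 | 19.4% vs 5% | 4.6 | 16% |
| 10% (5) | 0.8 | 35.3% vs 5% | 10.4 | 42% |
| 20% (10) | 0.3 | 10.2% vs 5% | 2.2 | 6% |
| 20% (10) | 0.5 | 14.6% vs 5% | 3.2 | 13% |
| 20% (10) | 0.8 | 22.2% vs 5% | 5.4 | 31% |
| 40% (20) | 0.3 | 8.1% vs 5% | 1.7 | 4% |
| 40% (20) | 0.5 | 10.1% vs 5% | 2.1 | 8% |
| 40% (20) | 0.8 | 12.3% vs 5% | 2.7 | 13% |

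For reference, intention to treat (50 vs 50 at 5%) rejects in 0.7% of trials. With ρ = 0 the odds ratio is 1.0 and the per-protocol comparison rejects in about 1%.

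**3. The limiting case.** If every remitter qualifies, remission among those kept is p / q. At q = 10% this is 0.05 / 0.10 = 50% and the test rejects in 67% of trials. At q = 20% it is 25% and 38%. At q = 40% it is 12.5% and 13%.

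**4. A second model.** In both arms a share w loses at least 10% of weight, and remission is r₁ in that group and r₀ otherwise. Two thirds meet the exercise condition, independently of remission. Overall remission is w·r₁ + (1 − w)·r₀, and the expected per-protocol difference is r₁ minus that.

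- w = 5%, r₁ = 30%, r₀ = 4%: overall 0.015 + 0.038 = 5.3%; difference about 25 points; rejects in 11%, against 0.8% for intention to treat.
- w = 10%, r₁ = 30%, r₀ = 3%: overall 0.030 + 0.027 = 5.7%; difference about 24 points; rejects in about 20%, against about 1%.

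Filtering on the exercise condition alone under this model gives about 2% to 3% rejection. The weight-loss criterion produces the inflation.

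**The case against.** The strongest reply has four parts.

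- **It is secondary.** The analysis takes one sentence, with no stated test or claim, and the primary analysis is by intention to treat. This stands and limits the severity.
- **The comparator is inferred.** The article does not say in words that all controls are used. That is true, but it restricts only one arm and gives controls no rule, so this is the plain reading. An analysis plan that is not shown could add detail. It could not remove the weight-loss criterion without contradicting the article.
- **Weight loss is not the only route.** The Discussion also credits exercise with directly lowering insulin resistance, and the Background cites HbA1c lowering independent of weight loss. So weight loss is a stated route, not the sole one. The selection remains biased as long as the two are related.
- **The null is artificial.** A trial in which the diet produces no more 10% weight loss than usual care is far from what is expected here. That is fair. The calculation shows that the comparison cannot separate effect from selection. It does not predict this trial's result.

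A reader might also infer that the per-protocol effect must always exceed the intention-to-treat effect. It need not. With no link between weight loss and remission there is no bias. In simulated null trials with a strong link (the two settings cited in the verdict), the per-protocol difference still failed to exceed the intention-to-treat difference in about 6% and 16% of evaluable trials.

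**Conclusion.** The point holds. As written, the rule selects intervention participants on a response to treatment, leaves controls unselected, and so favours the intervention. At 5% remission in both arms and no effect, the apparent odds ratio is about 1.7 to 10 and the test rejects in about 4% to 42% of trials (middle case 13%; 67% in the limiting case at q = 10%), against about 1% for intention to treat. These figures rest on assumed values of q and ρ, which the article does not give. The bias is largest when few qualify and the link is strong, and modest when 40% qualify (odds ratio at most about 2.7).

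Larger figures can be produced. With w = 15%, r₁ = 55% and r₀ = 4%, the second model gives a difference of about 43 points and 52% rejection. With 10%, 50% and 5% it gives about 40 points and 36%. But these imply control remission of 0.0825 + 0.034 = 11.7% and 0.05 + 0.045 = 9.5%, about twice the planned ceiling of 5%, with only about 5 and 3 participants kept. They should not be quoted as the expected size.

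Nor does the flaw reach the primary result. The change should be made, but the trial's main conclusion does not depend on it.

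**What to change.** - Remove the 10% weight-loss criterion from the per-protocol definition.
- Define the set by exposure to delivered components that the trial records, for example exercise sessions and dietitian visits attended. Session attendance is already needed for the planned exercise-adherence subgroups. The article describes no measure of meal-replacement use, so the definition should not depend on one unless it is being collected.
- Label the result supportive, because this is still a post-randomisation selection in one arm.
- Report remission among those losing at least 10% as a within-arm description, beside the planned breakdown by degree of weight loss, with no test against control.
- Optionally, add a complier-average estimate with randomisation as the instrument (intention-to-treat risk difference divided by the proportion adherent, with a confidence interval) as a sensitivity analysis. State that it assumes non-adherers gain nothing. In a diet-plus-exercise package, people who miss sessions may still follow the diet and remit, which would inflate the estimate. For illustration, 40 points with 50% adherent becomes 40 / 0.50 = 80 points.

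The cost is a change of wording and a per-protocol figure that is likely to be less favourable and less precise. The primary analysis and the sample size do not change.

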### Measurements

In-person evaluations occur before randomisation, at intervention period midpoint (12 weeks±1 week; no MRI study at this time point), and at intervention period end (24 weeks±2 weeks) (figure 1, table 1).

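### For continuous key secondary outcomes measured at weeks 12 and 24, one model of both visits would use the data better than the stated regression, given the planned loss of up to 30%

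*Protocol article*

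**What the plan says.** The Statistical analyses section of the protocol article names a method for each class of outcome.

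- Primary outcome: "We will apply intention-to-treat principles for the primary outcome, assuming that remission of diabetes did not occur if information is not available".
- Dichotomous secondary outcomes: handled like the primary.
- Continuous key secondary outcomes: "We will analyse continuous key secondary outcomes (eg, left ventricular peak early diastolic strain rate, lean soft tissue mass) through linear regression", or a log-linear version where suitable, with country and sex as strata. No intention-to-treat statement, missing-data rule or repeated-measures model is attached to this sentence.

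The Sample size section is open about the expected loss. The initial design reads "Allowing for up to 30% drop-out, we planned to recruit 80 individuals in total", and the current one "With an overall sample size of 100 (40 UK, 60 Canada), if 70 (70%) complete the trial". Power for peak early diastolic strain rate is also placed on completers: "Retention of at least 35 participants in each arm (70 total) will provide over 80% power".

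Table 1 marks most continuous key secondary outcomes at both week 12 and week 24: HbA1c, fasting glucose and insulin, HOMA-IR, weight, BMI, DXA fat and lean mass, VO2 peak, blood pressure, heart rate and lipids. Strain rate and end-diastolic mass to volume ratio are marked at week 24 only, and the Measurements section confirms that there is no MRI at the midpoint. The Withdrawal section stops evaluations as well as interventions, for reasons that include intolerance of the programme and adverse events.

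**The concern.** A regression of the week-24 value on arm can use only people who have a week-24 value. With up to 30 of 100 participants lost, the week-24 effects on HbA1c, weight, lean mass and fitness would be estimated in a subset formed after randomisation. Some of those lost will have attended at week 12, and that visit is usually the best available predictor of where they would have been at week 24.

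Two things are at stake. The first is precision, which is lost even if drop-out is random. The second is possible bias. Only the intervention arm has a demanding programme to leave, and the Withdrawal section ties the end of evaluations to intolerance of it. If those who have done poorly by week 12 tend to leave that arm, its completers look better than the arm as randomised. The dichotomous outcomes are treated differently, because the same missing participants are counted there as failures.

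**Working it through.** **1. The plan's own figures reproduce.**

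- Drop-out inflation: 56 / (1 − 0.30) = 80 and 70 / (1 − 0.30) = 100, as stated.
- Strain-rate power with 35 per arm, difference 0.10/s, SD 0.144, two-sided 5%: 0.10 / (0.144 × √(2/35)) = 2.905. The normal approximation gives Φ(2.905 − 1.960) = 82.8%, and the noncentral t gives 81.7%. Both are over 80%, as stated.
- With all 50 per arm observed, the t-test power would be 93.0%. The power statement is thus consistent with an analysis of completers.

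**2. What week 12 is worth: first simulation.**

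From the article: 50 per arm, 30% loss, outcome measured at baseline, week 12 and week 24. Assumed, not in the article: correlation of baseline with each follow-up 0.6; correlation of week 12 with week 24 0.8; true effects −1.0 SD at week 12 and −0.80 SD at week 24; 15% lost at random before week 12; 15% lost after it, with intervention-arm log-odds of loss rising by the slope shown per SD of poorer week-12 value. There were 5,000 trials per scenario. The completer regression has arm and baseline as covariates; the comparison is a likelihood estimate that also uses observed week-12 values.

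| Slope | Completer regression | 95% interval coverage | Likelihood with week 12 |
|---|---|---|---|
| 0 (random) | −0.796 | 94.8% | −0.797 |
| 1 | −0.870 | 93.8% | −0.802 |
| 1.5 | −0.890 | 91.7% | −0.799 |
| 2 | −0.904 | 90.8% | −0.798 |

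Completer bias at slopes 1 to 2 is 0.870 − 0.80 = 0.07 SD up to 0.904 − 0.80 = 0.10 SD, or 9–13% of the effect. With a standard error of about 0.19, that is 0.07/0.19 ≈ 0.4 to 0.10/0.19 ≈ 0.5 of a standard error. Under random drop-out the variance ratio is 1.10, so the standard error would fall by 1 − 1/√1.10 ≈ 5%.

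**3. Second simulation, with different assumptions.**

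True effect 0.7 SD (close to 0.10/0.144 = 0.69); baseline correlations 0.6 with week 12 and 0.5 with week 24; week 12–24 correlation 0.7 or 0.85; all of the intervention arm's 30% loss depends on the week-12 value when the slope is 1; the share of drop-outs with a week-12 value is 0, half or all. There were 3,000 trials per scenario.

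*Random drop-out: standard error in SD units, completer then week-12-informed.*

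- All seen at week 12: 0.213 to 0.203 at correlation 0.7 (1 − 0.203/0.213 ≈ 5%); 0.206 to 0.185 at 0.85 (≈ 10%).
- Half seen: 0.207 to 0.200 (≈ 3%); 0.207 to 0.194 (≈ 6%).

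Bias is nil to within simulation error for both methods.

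*Slope 1: bias in SD units, completer then week-12-informed.*

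| Share seen at week 12 | Correlation 0.7 | Correlation 0.85 |
|---|---|---|
| All | 0.109 → 0.005 | 0.141 → 0.000 |
| Half | 0.106 → 0.045 | 0.144 → 0.058 |
| None | 0.106 → 0.106 | 0.146 → 0.146 |

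**4. MRI outcomes.** With no week-12 scan they sit in the last row, so a repeated-measures model changes nothing. Borrowing from other week-12 measures is a separate matter. With an assumed correlation of 0.5 between a week-12 auxiliary and the week-24 MRI value, a bias of 0.07–0.09 SD falls to about zero. At 0.3, a bias of 0.03–0.04 SD also falls to about zero, with almost no gain in precision. The article gives no such correlation.

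**The case against.** The strongest reply is that the article never restricts the regression to complete cases. Linear regression is also the analysis step after multiple imputation, and missing-data handling for secondary outcomes is the sort of detail a condensed article leaves to a plan not shown here. The 35 per arm is a power assumption, not a definition of an analysis set. This stands as far as it goes. A reader might infer that the plan commits to dropping everyone without a week-24 value, but the text does not say so. What remains is a point about the method that is named: a regression not described as using both visits, for outcomes measured at both, with heavy loss planned.

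A reader might also infer that every continuous key secondary outcome is affected in this way. That fails for strain rate and mass to volume ratio. Strain rate is the first example in the quoted sentence and the only secondary outcome with a power statement. Nor are the week-12 data wasted: week 12 is an outcome time point in its own right, and later drop-outs count there.

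Finally, the simulations suit the remedy. In the first, loss is random or depends only on an observed week-12 value, so the likelihood estimate is bound to be nearly unbiased. The article's listed grounds for halting evaluations do not include poor week-12 response. The maintenance phase allows extra support after weight regain or reduced exercise, and controls are offered a diet programme only after final evaluations, which gives them a reason to stay. These are fair limits on the size of any bias. They do not affect the gain in precision.

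**Conclusion.** The point holds for the continuous key secondary outcomes measured at both visits. For these, the stated regression taken as written gives up about 5–10% in standard error, or about 3–6% in the second simulation when only half of drop-outs have a week-12 value. It could also bias the week-24 effect by about 0.07–0.14 SD if intervention-arm drop-out depends on week-12 response. Every one of these sizes rests on correlations, drop-out slopes and timing that the documents do not give.

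It would go too far to call the planned comparison biased. Under random drop-out it is not, and the article offers no evidence on which mechanism will operate. Nor is the alternative a complete cure: with half of drop-outs unseen at week 12, 0.05–0.06 SD of bias remained. Missing at random also treats drop-outs as following the course of continuing participants in their arm with the same observed history, which may be optimistic for people who stop the programme.

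The improvement is modest and confined to secondary outcomes.

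**What to change.** State that continuous key secondary outcomes measured at weeks 12 and 24 will be analysed as randomised in one longitudinal likelihood model (a mixed model for repeated measures). The week-12 and week-24 values are the responses, on the log scale where appropriate, adjusted for baseline, country and sex, with arm-by-visit terms and the treatment effect read at week 24. Report the completer regression as a sensitivity analysis.

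For the MRI outcomes, keep the single-visit regression. Multiple imputation using week-12 weight, HbA1c and VO2 peak is optional, and its benefit depends on correlations not yet known.

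The cost is a sentence or two in the plan and slightly more analysis work, on data already being collected. The model relies on missing at random given the observed visits, which is a weaker assumption than the one the completer regression makes.
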